### Trial design

The design of the planned bi-centric randomized controlled superiority trial will be based on a within-between interaction group design with three groups (WLC, APP, TG-APP) and parallel group assignment. The primary outcome criterion is the change in symptom severity of SAD, as measured by the Liebowitz Social Anxiety Scale (LSAS) [21, 22]. It will be assessed by trained, blinded, independent raters at pre-treatment, post-treatment, and 6 months after post-treatment (follow-up). The planned allocation ratio for TG-APP vs. APP only vs. WLC will be 1:1:0.7.

## Methods

### Design and sample size

We conducted a simulation-based a priori power analysis for a 3 × 2 interaction (group ( time) in a linear mixed model for the primary outcome of SAD symptom severity (according to the LSAS), using the R package “simr” [23]. The analysis is based on a model including a random intercept for participants, a moderate effect size of Cohen’s *d* = 0.5 for the treatment effect in the APP condition, and a large treatment effect of Cohen’s *d* = 0.8 for the TG-APP condition compared to the control group (implying a small effect in favor of TG-APP between both treatment conditions).

We chose these effect sizes as conservative estimates based on the results of a recent meta-analysis reporting moderate effect sizes in ICBTs for SAD [12]. Comparable to Stolz et al. [16], we decided to recruit different sample sizes for the control and treatment conditions, because treatment effects compared to the control group were assumed to be larger than between the two treatment conditions.

We based our power analysis on an iterative simulation of increasing sample sizes with starting values of *n* = 30 for the control condition and *n* = 50 for each of the treatment conditions, increasing stepwise by one participant per condition. The variance of the random intercepts and residual variance was set to 0.5 respectively [24]. Because missing values due to the dropout of participants were planned to be imputed by the jump to reference method (J2R) [25], the reference being the control condition, we reduced our expected effected sizes by multiplying them with the term (1—dropout-rate). Given a dropout rate of 26% at post-treatment evaluation in the study by Stolz et al. [16] and a pooled post-treatment dropout rate of 26.2% in a meta-analysis of studies using smartphone apps by Torous et al. [26], we chose a conservative estimate of 30% post-treatment dropout for the APP condition and multiplied the expected effect size of 0.5 by 0.7, equaling to *d* = 0.35. For the TG-APP condition, we expected a lower post-treatment dropout rate of 20% due to the additional guidance by a therapist and multiplied the expected effect size of 0.8 by 0.8, equaling to *d* = 0.64. Based on 500 simulations of the linear mixed model fitted with the expected effect sizes, we obtained the power of finding a statistically significant interaction of group × time based on a likelihood ratio test, compared to finding only main effects, and the 95% confidence interval for this estimate, for increasing sample sizes. We located the minimum sample size in our results after which the lower bound of the 95% confidence interval did not fall below 80% power, given *α* = 0.05. This condition was met at *n* = 41 for the control group and *n* = 61 for both treatment conditions (power estimate = 84%, 95% confidence interval = 80.0, 87.0). In addition to our study purposes, the app provider intends to use the results of the pilot study and the main study for the licensing process of the app as a digital health product. For this licensing process, a separate statistical analysis will be conducted comparing only the APP condition with the WLC condition, using a *t*-test for statistical analysis. A corresponding additional sample size calculation revealed the need to recruit 43 subjects in the wait-list control group (WLC). To establish conformity across the planned analyses we adjusted the number of participants for WLC upward to *n* = 43, resulting in a total sample size of *N* =165 (see also Fig. 1).

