#### Drop-out analyses

We define as “drop-out” any participant who did not complete the post-treatment measurement. Systematic differences in dropout rates between the three groups will be analyzed by a Fisher exact test. In addition, differences between participants and drop-outs in terms of sociodemographic and clinical variables will be considered.

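### The stated 84% power treats every simulated patient as observed: it allows for no wait-list dropout and leaves out the effect of imputation on the test's variance

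*Protocol article*

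**What the plan says.** Under Design and sample size, the protocol article powers the trial for a "statistically significant interaction of group × time based on a likelihood ratio test". It is a 3 × 2 test of change from baseline to post-treatment in the LSAS. The simulation settings are given: "The variance of the random intercepts and residual variance was set to 0.5 respectively".

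Dropout is handled through the planned J2R imputation, with the control arm as reference: "we reduced our expected effected sizes by multiplying them with the term" one minus the dropout rate. For APP, "we chose a conservative estimate of 30% post-treatment dropout for the APP condition", and the authors "multiplied the expected effect size of 0.5 by 0.7, equaling to" 0.35. For TG-APP, 20% dropout takes 0.8 to 0.64. No rate is given for WLC.

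The sample size was the smallest after which "the lower bound of the 95% confidence interval did not fall below 80% power, given *α* = 0.05". This was met at 41 WLC, 61 APP and 61 TG-APP ("power estimate = 84%, 95% confidence interval = 80.0, 87.0"). WLC was later raised to 43 for a separate licensing analysis, giving N = 165. The Allocation and randomization section randomises exactly 43/61/61, so the active arms carry no inflation for dropout.

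Two other sections bear on this. Drop-out analyses plans to test "Systematic differences in dropout rates between the three groups", so WLC dropout is treated as possible. Primary analysis describes a random-intercept mixed model and does not mention imputation.

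**The concern.** J2R dropout has two consequences for power. It pulls the mean effect towards the reference arm, and it changes the variance of the estimated effect and of the test built on it. The discount on the effect sizes covers the first. The second is absent, because the simulated data sets are complete.

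WLC loss is absent as well, although WLC is the smallest arm and also the arm from which active-arm dropouts are imputed.

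At stake is the rule by which N was fixed. The authors required the lower confidence limit for power to reach 80%, and it does so only just, at 80.0. Any uncounted loss of a few points defeats that rule.

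**Working it through.** **Inputs from Design and sample size.** Alpha is 0.05, and the test is a likelihood ratio test on 2 df. Residual variance is 0.5. Effects are 0.5 and 0.8 before the discount, 0.35 and 0.64 after it. Dropout is 30% in APP and 20% in TG-APP. **Assumption:** WLC dropout of 0-30%, since the article gives none.

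**Step 1: reproduce the stated figure.** With two time points and a random intercept, the interaction test compares mean change across three groups. The variance of a change score is 2 × 0.5 = 1. At 41/61/61 the noncentrality is

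λ = 61 × (0.35² + 0.64²) − (61 × 0.99)² / 163 = 32.458 − 22.374 = 10.084.

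The noncentral chi-square on 2 df gives power of 81.9%; direct simulation of the likelihood ratio test (100,000 runs) gives 81.8%. The stated interval fits about 418 successes in 500 (83.6%, exact interval 80.1 to 86.7), so 81.9% agrees within the error of 500 runs. At 43/61/61, λ = 32.458 − 60.39²/165 = 10.355 and power is 83.0%. Both results need every post-treatment value to be observed.

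**Step 2: check the discount.** Data were simulated with effects of 0.5 and 0.8, random dropout of 30% and 20%, and J2R imputation. The pooled effects were 0.352 and 0.641 (43 WLC, no WLC dropout). The multiplication by one minus dropout is therefore correct for the mean.

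**Step 3: look at the variance.** With complete data, the standard error of an active-versus-WLC contrast is √(1/43 + 1/61) = 0.199. Under J2R with no WLC dropout, Rubin's rules give 0.221 (APP) and 0.215 (TG-APP), both larger. The actual standard deviation of the same estimates over repeated trials is 0.186 and 0.193, both smaller. Whether power falls below or rises above the complete-data figure therefore depends on which variance the test uses.

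**Step 4: power at 43/61/61** (6,000 trials, 50 imputations; the Rubin column spans the pooled F test and the total-variance Wald test).

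| WLC dropout (assumed) | Multiple imputation, Rubin's rules | Single imputation, treated as observed | Actual sampling variance |
|---|---|---|---|
| 0% | 75-77% | 81% | 86% |
| 10% | 74-76% | 81% | 84% |
| 20% | 73-74% | 80% | 83% |
| 30% | 72% | 79% | 80% |

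With no true effect and 20% WLC dropout, type I error was about 2% under Rubin's rules and 6.9% under single imputation. Repeat runs with fewer imputations and trials moved entries by a few points, down to 70% in the Rubin column (30% WLC dropout) and up to 91% in the last column (none). I read the three columns as about 72-78%, 78-81% and 80-90%.

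**Step 5: the mixed model with no imputation.** If observed data alone are analysed under missing at random, the undiscounted effects apply to 43/42.7/48.8 patients:

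λ = 42.7 × 0.25 + 48.8 × 0.64 − 60.39²/134.5 = 41.907 − 27.115 = 14.792.

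Power is 94%. With 30% WLC dropout (30.1 patients), λ = 41.907 − 60.39²/121.6 = 11.916 and power is 88%.

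**The case against.** The strongest reply is that nothing printed is miscalculated. The two products are right, the discount is the correct J2R adjustment of the mean, and the stated power is reproduced. J2R also gives every randomised patient a value, so keeping 61 per active arm is not in itself a mistake. All of this stands.

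A second reply is that the low figures depend on multiple imputation with Rubin's rules, which the article never names. Rubin's variance is conservative under J2R: borrowing from the reference arm reduces the real variability of the estimate, and Rubin's rules do not credit that. Type I error near 2% shows that part of the shortfall comes from an over-cautious test. This also stands. It is why a reader who infers that true power is below 80%, or that 84% should simply be replaced by a figure in the low 70s, goes further than the documents allow.

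A third reply is that the WLC rate and the variance method may sit in a fuller protocol or analysis plan. That answers a complaint about missing detail, but not this one. The power calculation is in the article; it invokes J2R, applies one of its two consequences, gives dropout for two arms of three, and reports 84% without condition.

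Finally, 30% APP dropout exceeds the cited 26% and 26.2%, and the effect sizes are called conservative. That is some cushion for the assumed effects, but it does not supply the omitted variance or WLC loss.

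**Conclusion.** The concern holds in a limited form. The 84% is a complete-data figure with the active effects shrunk. It allows for no WLC dropout and ignores what imputation does to the test.

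Under the usual way of running J2R (multiple imputation with Rubin's rules), power at N = 165 is about 72-78%, below the 80% target even if no WLC patient is lost. With single imputation treated as observed data it is about 78-81%, and type I error can exceed 5%. With a variance that tracks the estimator's real variability it is about 80-90%, which meets the target.

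These ranges rest on random dropout at the article's own active-arm rates, on completer effects of 0.5 and 0.8, and on an assumed WLC range of 0-30%. The documents do not settle which variance method applies. They also leave open whether J2R belongs to the primary model: the Primary analysis section does not mention it, though it does not exclude it either. If J2R is not used, the discounted effects lose their basis and power is about 88-94%. The defect is therefore an unconditional figure that its own premises do not determine; it does not show that the trial is too small.

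**What to change.** 1. State an expected WLC dropout rate beside the 30% and 20%.
2. State whether J2R is single or multiple imputation and how the variance of the effect is obtained.
3. Reconcile Design and sample size with Primary analysis, so that it is clear whether the primary mixed model is fitted to J2R-imputed data.
4. Rerun the simulation at 43/61/61. Generate completer effects of 0.5 and 0.8, delete post-treatment values at the stated rates in all three arms, then impute and test exactly as planned. Check type I error in the same run.
5. Replace the unconditional 84% with the power at N = 165 from that run. Expect about 72-78% if Rubin's rules are used.

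The cost is a rerun of the existing simulation with an added imputation step, a few sentences of text, and possibly a less favourable stated power. No extra recruitment is needed.

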
**Fig. 1 Fig1:**
[figure not shown]
Study flowchart

As a robustness check, we additionally conducted a power analysis based on the simulation of a 3 × 3 interaction (group × time) that included the estimated effect sizes at *t*_3_ (follow-up assessment), for which we obtained a highly similar sample size.

### Procedure

The study will be conducted in Germany at the outpatient psychotherapy unit of the Clinical Psychology department of the Goethe University of Frankfurt as well as the outpatient psychotherapy unit of the Clinical Psychology department of the Technische Universitaet Dresden and two further CBT training centers in Dresden. For reporting purposes, we followed the SPIRIT reporting guidelines [27].

In the first step, all persons that register for participating in the study will be screened using an online self-report assessment. If participants exceed the cut-off of 25-points or find themselves within the criteria for social anxiety disorder, they are referred to another online self-assessment and then invited for an interview with a clinical rater. Beforehand, they will be informed about the study and provided with written informed consent (either personally or via email if necessary). Interviews to determine the patient's formal diagnosis are conducted by blinded and independent psychologists (with at least a master’s degree) who have been trained in the appropriate interviews. Eligible patients are then randomly assigned to one of three groups (WLC, APP, TG-APP). Participation in each of the groups lasts 3 months. Participants in the WLC group then have the option of using the app if they wish. The outcome measures will be assessed by blinded and independent raters at baseline, post-treatment (3 months after start), as well as 6 months after the post-treatment interview (follow-up). Furthermore, participants will complete self-report questionnaires online at baseline, at mid-treatment (at 6 weeks), post-treatment (at 12 weeks), and follow-up (at 36 weeks; see Fig. 1 for the study flowchart). Interviewers will remind patients to fill out the self-report questionnaires and if necessary, patients will be contacted by the study coordinator to complete the missing questionnaires.

Prior to the start of the study, we will conduct a pilot study to improve usability and evaluate the mobile application and the applicability of therapist-guided video therapy and the videoconferencing tool.

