### Objectives

The main goal of the present study is to evaluate whether the use of the app-based intervention helps to decrease symptoms of social anxiety disorder and has positive effects on mental health. There will be two experimental treatment conditions: App-based CT (APP) and app-based CT plus 8 therapist-guided video-delivered therapy sessions (TG-APP). Both will be compared to a wait-list control group (WLC). The therapists will be trained in Cognitive Therapy based on the model of Clark and Wells [4], which has been proven to be effective in face-to-face therapy [5] and in ICBT [15]. In a randomized controlled trial (RCT), the following hypotheses will be tested:Hypothesis 1a: In the APP and TG-APP condition, SAD-related symptoms, as measured by the LSAS, will decrease significantly more from baseline to post-treatment than in the WLC condition.Hypothesis 1b: The TG-APP condition results in a significantly greater reduction in SAD-related symptoms, as measured by the LSAS, than the APP and the WLC conditions, from baseline to post-treatment.Hypothesis 1c: In the APP and the TG-APP condition, there will be no significant deterioration of SAD-related symptoms, as measured by the LSAS, from post-treatment to follow-up.Hypothesis 2a: In the APP and TG-APP conditions, significant improvements in secondary outcome variables, including social phobic cognitions, depression symptoms, general psychological distress, psychological impairment, quality of life, and interpersonal pleasure, are achieved from baseline to post-treatment compared to the WLC condition.Hypothesis 2b: In the TG-APP condition, improvements in secondary outcome variables from baseline to post-treatment will be significantly larger than in the APP condition.Hypothesis 2c: In the APP and TG-APP condition, there will be no significant deterioration in secondary outcome variables from post-treatment to follow-up.Hypothesis 3: Individual learning styles contribute significantly to predicting success in both treatment conditions.Hypothesis 4: The increase in social approach behavior will mediate the effect of the TG-APP versus APP condition.

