Treatment satisfaction will be measured by using the Client Satisfaction Questionnaire (CSQ) [50], which we adapted slightly to match the use of the app. This 8-item questionnaire uses questions like “How satisfied are you with the amount of help you received?“. It showed satisfying internal consistency and concurrent validity [51, 52]. Social anxiety and social approach behavior will be measured using a modified version of the Social Phobia Weekly Summary Scale (SPWSS) [53], which will be assessed by participants weekly (for the APP and the TG-APP condition) and at pre, mid, post and follow-up assessments (for all conditions). The SPWSS covers ratings of anxiety, avoidance, self-focused attention, anticipatory worry, post-event rumination, and social approach behavior. We added questions asking for feelings of pleasure and pursuit of personal goals and changed the scale to a 0–100 scale. The SPWSS is sensitive to treatment effects and has good internal consistency [53].

Finally, we will also assess negative side effects which are specific to patients with SAD. Drawing on the results of Boettcher et al. [19], we developed a brief (7-item) scale with items covering the negative side effects that were considered most relevant by a group of experts (see Additional file 1). The items are rated on a scale from 0 (“do not agree at all”) to 5 (“fully agree”). Please note that the descriptive list of possible side effects is preliminary and may be slightly revised after the pilot study. As the list contains an open item, responses to this item will be evaluated after the pilot study and inclusion of further side effects in the list is possible should they be mentioned frequently.

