#### Secondary analyses

As secondary analyses, we will evaluate treatment effects (from baseline to post-treatment, as described in hypothesis 2a and from post-treatment to follow-up, as described in hypothesis 2c) on quality of life, as measured by the WHO-QOL-BREF, interpersonal pleasure, as measured by the ACIPS, further SAD-related symptoms, as measured by the SPIN and the CGI, social phobic cognitions, as measured by the SPK, symptoms of depression, as measured by the BDI-FS and the QIDS-C, general psychological distress, as measured by the BSI, and limitations in everyday life, as measured by the PDI. We will also assess adverse effects measured by the self-developed adverse effect scale. Moreover, we will compare posttreatment LSAS scores with scores at follow-up, as stated in hypothesis 1c, using the linear mixed model described earlier.

To control for moderating effects on decreases in social anxiety symptoms, as indicated in hypothesis 3, we include the scores of the individual learning style, as measured by Kolb’s LSI and experienced pain in social situations, as measured by the SPQ-5, as predictors in the model and specify three-way interactions with treatment conditions and time for all these factors. We will conduct a similar analysis to test whether social approach behavior measured by the SPWSS has a mediating effect on social anxiety symptoms, as we hypothesized in hypothesis 4. We will test all interactions by comparing the full to a reduced model without the respective interaction term via likelihood ratio tests (LRTs) [62] and remove all non-significant interactions from the final model.

To evaluate effects between two conditions at a given time, e.g., between the APP and TG-APP conditions at post-treatment, as indicated in hypothesis 1b and 2b, we will calculate the statistical significance of pairwise differences in LSAS based on the linear mixed model using the R package “emmeans” [63].

We will fit all measures as outcome variables in linear mixed models including the same predictors as in the primary analysis and add the average weekly time participants spent using the app and the number of behavioral experiments conducted as additional explanatory predictors.

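### Wait-list participants may use the app from month 3, yet the all-arm model and the J2R control reference are not limited to the period before that, which leaves the follow-up results (H1c/H2c) open to wait-list improvement

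*Protocol article*

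**What the plan says.** **Control period and follow-up.** Under Procedure: "Participation in each of the groups lasts 3 months". Then: "Participants in the WLC group then have the option of using the app if they wish". Outcomes are rated at baseline, at post-treatment, "as well as 6 months after the post-treatment interview (follow-up"). Follow-up therefore falls wholly after WLC gains access to the app. For the weekly summary scale (SPWSS), the section on self-rating scales says that data are collected "at pre, mid, post and follow-up assessments (for all conditions").

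**Hypotheses.** H1c reads: "In the APP and the TG-APP condition, there will be no significant deterioration of SAD-related symptoms", from post-treatment to follow-up. H2c says the same for the secondary outcomes. Neither names WLC.

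**Analysis.** Primary analysis specifies a random-intercept model with time, condition and their interaction. Secondary analyses evaluates treatment effects "from post-treatment to follow-up, as described in hypothesis 2c" and tests H1c with that same model. It gives the other outcomes the same predictors. No arm is excluded at any time point. The section also says that all interactions are tested by likelihood ratio and that non-significant ones are removed.

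**Imputation.** Under Design and sample size, missing values due to drop-out were "planned to be imputed by the jump to reference method (J2R) [25], the reference being the control condition".

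**Power.** N = 165 comes from a 3 × 2 simulation (baseline and post-treatment) and a separate *t*-test for licensing. A robustness check used a "power analysis based on the simulation of a 3 × 3 interaction (group × time) that included the estimated effect sizes at" follow-up. Those effect sizes are not reported.

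**The concern.** Randomisation gives an untreated comparator for three months only. After that, WLC participants decide for themselves whether to take the same app, so WLC at follow-up is a mixture of treated and untreated people.

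The article does not carry this through to the follow-up analysis. It keeps WLC in the model, does not limit its use as imputation reference to the first three months, and has an interaction-removal rule that could merge its time course with that of the active arms. Each of these can bring WLC's app-driven improvement into results that are meant to show whether APP and TG-APP hold their gains. The direction depends on the route. J2R and pruning favour a finding of no deterioration. Reading the interaction as a treatment effect can suggest that benefit was lost when nothing changed in the active arms.

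**Working it through.** **Inputs from Design and sample size.** Random-intercept variance 0.5 and residual variance 0.5, so the total SD is 1 and a change score has variance 2 × 0.5 = 1.0. Effects after dilution are 0.35 (APP) and 0.64 (TG-APP). The undiluted app effect is 0.5. Drop-out is 30% (APP) and 20% (TG-APP). Arms are 41/61/61 in the simulation and 43/61/61 as randomised (WLC/APP/TG-APP).

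**Assumptions not in the document.** WLC uptake *u* is not given; 50% is the main case and 100% the extreme. The app effect *a* in WLC users is 0.35 to 0.5 SD. WLC's gain from post-treatment to follow-up is then *u* × *a*, or 0.175 to 0.25 SD at 50% uptake.

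**The plan's own figure first.** For the 3 × 2 test the noncentrality is Σn(m − m̄)²/1.0. With m̄ = 61 × (0.35 + 0.64)/163 = 0.3705, it is 61 × (0.35² + 0.64²) − 163 × 0.3705² = 10.08. Power on 2 df is about 82%. The article reports 84% with interval 80.0 to 87.0, so the model set-up is confirmed within simulation error.

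**Case (a): J2R carried to follow-up.** Imputed drop-outs follow the WLC mean, so the arm mean moves by drop-out × *u* × *a*:

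- APP: 0.30 × 0.175 = 0.05 SD to 0.30 × 0.25 = 0.075 SD
- TG-APP: 0.20 × 0.175 = 0.035 SD to 0.20 × 0.25 = 0.05 SD

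At 100% uptake these become 0.105 to 0.15 SD and 0.07 to 0.10 SD. As a rough guide, the standard error of a within-arm change is √(1.0/61) = 0.128. Power to detect an arm-mean worsening of 0.30 SD in APP is about 65%. With a 0.075 SD masking shift it is about 42%.

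**Case (b): the post-to-follow-up group × time term read as a treatment effect.** Let APP and TG-APP be perfectly stable and only WLC change. The noncentrality is (*ua*)² × 43 × 122/165 = (*ua*)² × 31.79.

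| Uptake | WLC gain (SD) | Noncentrality | Chance of significance (2 df, α = 0.05) |
|---|---|---|---|
| 0% | 0 | 0 | 5% |
| 50% | 0.175 to 0.25 | 0.97 to 1.99 | 13% to 22% |
| 100% | 0.35 to 0.5 | 3.89 to 7.95 | 41% to 72% |

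**Case (c): interaction removed.** The common post-to-follow-up time effect is an average over all arms, so WLC contributes 43/165 of its gain: 43/165 × 0.175 = 0.046 SD to 43/165 × 0.25 = 0.065 SD at 50% uptake, and 0.09 to 0.13 SD at 100%. On the planned effects the three-time-point LSAS interaction is significant about 78% of the time at 50% uptake, so it would be removed about 22% of the time.

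**The 3 × 3 robustness check.** It cannot be reproduced because its follow-up inputs are not given. Holding the post-treatment effects at follow-up, its noncentrality at 41/61/61 is 10.08 × (2/3)/0.5 = 13.4, with power about 85%; at 43/61/61 it is also about 85%. At 50% uptake and 43/61/61 it is about 78%. The loss is modest because the baseline-to-post-treatment contrast still carries the test.

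**What does not move.** With the full interaction kept and no J2R at follow-up, the APP and TG-APP post-to-follow-up contrasts come from those arms' own means. WLC uptake does not shift them.

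**The case against.** The strongest reply is that H1c and H2c are worded within APP and TG-APP, and that no section plans a post-to-follow-up contrast against WLC. A reader might infer that a stable APP arm will be reported as having deteriorated relative to WLC. That contrast is not in the document, and the direct within-arm contrast on observed data is sound. This part of the reply stands.

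Three further points also stand:

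- The trial is not sized on a follow-up comparison with WLC. N = 165 rests on the 3 × 2 simulation and the licensing *t*-test, and the 3 × 3 run is only a robustness check.
- J2R at follow-up is an inference. The J2R text sits in the sample-size rationale beside post-treatment drop-out rates. The inference is reasonable, because the analysis set is everyone randomised and people who miss post-treatment will usually miss follow-up too, but it is not stated.
- Follow-up data in all arms are explicit only for the SPWSS. That WLC receives the follow-up LSAS rating is the natural reading of Procedure, but it is not stated arm by arm, and the schedule figure is not available here.

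It could also be said that visit-level imputation and contrast coding belong in the SAP. That answers less. The article goes beyond silence: it names the reference arm, reuses the all-arm model after access opens, and sets a removal rule for all interactions. As written, those statements permit all three cases.

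**Conclusion.** The concern holds in a limited form. At follow-up WLC is no longer an untreated control, and the stated follow-up analysis does not allow for that. H1a and H1b at post-treatment, the sample size, and direct within-arm H1c/H2c contrasts on observed data from the full-interaction model are unaffected.

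The follow-up results are exposed only if J2R is carried to follow-up, if the post-to-follow-up interaction is read as a treatment effect, or if the interaction is removed. These are alternative routes and should not be added into one bias. All sizes rest on the assumed uptake and on an app effect of 0.35 to 0.5 SD in WLC users; at zero uptake all three vanish. The broader reading, that the follow-up analysis will mislead on H1c/H2c whichever way it is run, goes further than the document supports. The point should be settled before follow-up data are analysed, but it does not threaten the primary result.

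**What to change.** Leave the WLC option to use the app as it is, and change the analysis wording:

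1. State that H1c and H2c are tested by within-arm post-to-follow-up contrasts in APP and TG-APP, plus TG-APP versus APP, with the condition × time interaction retained whatever its significance.
2. Limit inferential comparisons with WLC to baseline and post-treatment. Record app use in WLC and report its follow-up data descriptively by app use.
3. State that WLC data after month 3 are not used as the J2R reference. Own-arm imputation, or holding the WLC post-treatment level, are two ways to do this.
4. Give the WLC follow-up assumption behind the 3 × 3 robustness check, or rerun it with a stated uptake.

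The cost is protocol or SAP wording and at most one simulation rerun, with no extra patients or visits. The downside is that the trial gives up an inferential comparison with WLC at follow-up, which would not be valid as an untreated comparison anyway.
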